### 2.6. Blinding

Blinding of the investigators will not be required, since the trial outcomes will be based on objective quantitative data from stool and laboratory tests, mitigating any impact from unblinding. The patients will not be blinded because of the nature of the trial.

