### 2.3. Participants

All patients with rectal cancer who visit our outpatient clinic will be closely monitored to ensure their eligibility. Once eligibility is confirmed, the surgeon responsible for each included patient will explain this study during their outpatient clinic visit and obtain informed consent.

Given the absence of previous studies examining changes in the gut microbiota of the resting colon following ileostomy reversal, a sample size calculation was not performed. Therefore, this study was designed as a pilot trial, and we anticipated that a sample of 20 patients would be sufficient to assess the changes in microbiota based on the intake of probiotics after ileostomy repair. According to the order of patient enrollment, the first 10 consecutive patients will be assigned to the probiotic group, while the next 10 patients will be assigned to the control group. The participants will be enrolled by the surgeon at each outpatient clinic, and probiotics will be provided by a designated researcher.

At the initial outpatient visit, an assessment will be conducted to confirm eligibility based on the inclusion criteria, followed by obtaining informed consent. All patients will undergo rectal resection with loop ileostomy as previously performed. The timing of ileostomy reversal will be determined based on the necessity of chemotherapy. The first fecal test will be performed before rectal resection, and the second fecal test will be performed during the first bowel movement after ileostomy repair. Patients in the experimental group will take probiotics for 3 weeks starting from the second fecal test, whereas patients in the control group will be observed for 3 weeks without taking probiotics. Afterward, the third fecal test will be performed at the next outpatient visit. Additionally, blood tests, including complete blood count (neutrophil, monocyte, lymphocyte, hemoglobin, and platelets), albumin, and C-reactive protein, will be performed to identify changes in inflammatory markers. Table 1 demonstrated the comprehensive schedule of assessments.

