### 2.5. Outcomes

The primary outcome is changes in the gut microbiota based on the intake of probiotics at the following time points: before bowel resection, immediately after diverting stoma repair, and 3 weeks after diverting stoma repair. Genomic DNA will be extracted from bacterial samples in patients’ feces using the QIAamp DNA Stool MiniKit (Qiagen^®^, Hilden, Germany). The library will be prepared according to the 16S Metagenomic Sequencing Library Preparation Illumina Protocol. Amplification of the V3–V4 region of 16S rRNA will be performed, followed by a polymerase chain reaction. After the quality assessment of the final library, the DNA quantity will be determined using the Qubit (Thermo Fisher Scientific Inc., Waltham, MA, USA) and Agilent Bioanalyzer 1000 (Agilent, Santa Clara, CA, USA). The methods for fecal microbiota analysis will follow a previously established procedure [25]. The EZBioCloud (ChunLab, Inc., Seoul, Republic of Korea) will be used to analyze the metagenome. To evaluate within-sample richness and evenness, the Shannon and Simpson indices will be applied, while dissimilarities between samples will be assessed using the Jensen–Shannon divergence and generalized UniFrac distance. We will analyze the pattern of changes to evaluate whether a 3-week course of probiotics alleviates dysbiosis, observed after ileostomy repair, and how it differs from the gut microbiota composition identified prior to the initial surgery. Alpha- and beta-diversity analyses will be conducted, along with an assessment of the proportions of beneficial and harmful bacteria [10].

The secondary outcomes include changes in inflammatory markers and differences in gut microbiota composition based on chemotherapy. Changes in inflammatory markers will be analyzed by comparing various ratios of neutrophils, lymphocytes, albumin, and C-reactive protein. The relationship between probiotic intake and inflammatory markers will be examined to explore the potential anti-inflammatory effects of probiotics following ileostomy repair. Additionally, gut microbiota composition will be compared between patients who underwent chemotherapy before stoma repair and those who did not.

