### 2.7. Data Collection and Management

All investigators will receive uniform annual training to ensure consistent assessment. A professional company performing laboratory work on fecal microbiota tests will ensure high reliability and validity. Detailed contact preferences will be collected, followed by text messages before follow-up visits to promote participant retention. A participant will be considered lost to subsequent assessment after a maximum of four contact attempts have been made.

The researcher responsible for outcome management will enter data into paper-based case report forms (CRFs). The CRF data will be meticulously reviewed for completeness and accuracy. Any discrepancies identified during the review will be resolved by the principal investigator’s verification. All CRFs will be stored in a locked, secure location accessible only to research team members. Furthermore, regular audits will be conducted to monitor access and ensure compliance with security protocols. The participant’s personal information will be protected by assigning a study identification number not associated with their identity.

The collected stool samples will be safely stored at the designated company. Upon additional request within a specified period, the following analyses can be performed and utilized in future research: calprotectin analysis using enzyme-linked immunosorbent assay, characterization of short-chain fatty acids through gas chromatography-mass spectrometry analysis, and β-glucuronidase activity analysis using fluorescence assay.

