A limitation of this protocol is that participants are allocated sequentially rather than randomized. While this method is pragmatic for a small, single-center pilot trial, it carries the potential for selection bias and confounding, which should be acknowledged when interpreting the findings. A further limitation is that the intervention is a commercially available multi-component synbiotic product containing not only probiotics but also prebiotics, vitamins, and minerals. Therefore, the effects cannot be attributed exclusively to probiotics; however, this formulation was chosen because it reflects actual clinical practice and has been utilized in previous clinical studies. In addition, the absence of placebo and blinding may introduce additional bias despite the use of objective outcome measures. This limitation reflects the exploratory design of this protocol and indicates that future randomized, placebo-controlled trials will be essential to validate and expand upon our findings. Finally, dietary intake was not strictly controlled, which may have influenced gut microbiota composition despite advising participants to maintain their usual habits.

To our knowledge, this is the first prospective cohort trial to investigate changes in gut microbiota based on oral probiotic administration in patients undergoing diverting stoma repair. The findings of this trial may offer a theoretical basis for understanding the effects of probiotics on dysbiosis during diverting stoma repair. Moreover, the results may offer insights that can inform perioperative management strategies and contribute to developing microbiota-targeted interventions to improve postoperative recovery in colorectal cancer patients.

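### Section 2.6 drops investigator blinding because outcomes are objective, while the Discussion concedes bias despite objective outcomes; reconcile the two and mask sample codes, run order and the analyst

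*Protocol article*

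**What the plan says.** **Blinding rule.** Section 2.6 of the protocol article reads: "Blinding of the investigators will not be required, since the trial outcomes will be based on objective quantitative data from stool and laboratory tests", with the stated consequence "mitigating any impact from unblinding". Patients are open-label on a separate ground: "The patients will not be blinded because of the nature of the trial". The laboratory and the analyst are not named.

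**Limitations.** Protocol article, 3. Discussion: "the absence of placebo and blinding may introduce additional bias despite the use of objective outcome measures".

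**Laboratory and coding.** In 2.7 the stool assay is placed with an outside company: "A professional company performing laboratory work on fecal microbiota tests will ensure high reliability and validity". Participants are protected by "assigning a study identification number not associated with their identity". That measure is presented as privacy protection; the section does not say whether the code hides the arm.

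**Allocation.** In 2.3, "the first 10 consecutive patients will be assigned to the probiotic group, while the next 10 patients will be assigned to the control group".

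**Outcomes and tests.** In 2.5, for diversity within a sample, "the Shannon and Simpson indices will be applied"; two further measures cover dissimilarity between samples. None of the four is named as leading. The same section adds the share of beneficial and harmful bacteria (a citation is given, the taxa are not listed) and, as a secondary outcome, unnamed ratios of four blood markers. Section 2.8 allows a t-test or a Mann–Whitney test for continuous variables without a rule for choosing, with 0.05 as the threshold throughout.

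**The concern.** The Methods and the Discussion give opposite answers to one question: do objective measurements dispose of the concern about knowing the arm? The reason 2.6 relies on is the reason the Discussion calls insufficient.

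Sequence counts and blood values are indeed hard to influence by expectation. The arm comparison is built from them by later decisions: taxa lists, ratios, measure to emphasise, test. If those decisions are made by people who know the arm, they can drift towards a favoured result.

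The 10-then-10 allocation sharpens this in two ways. Anyone who sees enrolment order or dates can infer the arm, so an ordinary study number may conceal nothing. And if stools were sequenced in order of arrival, which the article does not say, run and storage time would tend to line up with arm. A technical difference could then look like a product effect in the primary outcome.

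**Working it through.** The article gives no figure to reproduce here. The core of the check is a comparison of texts; the arithmetic only shows scale under assumptions.

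**1. The two statements side by side.** Section 2.6: blinding not needed for investigators, because the data are objective and this deals with any impact. Discussion: bias possible although the measures are objective. To mitigate can mean only to reduce, so this is not a strict logical contradiction. But covering any impact, and concluding that blinding is not required, goes further than the Discussion allows.

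**2. Does objectivity carry the argument?** Section 2.5 leaves four diversity measures without a leading one, taxa unlisted in the article, and ratios of four blood markers (4 × 3 / 2 = 6 possible pairs). Section 2.8 leaves the test open. An objective assay does not settle any of these choices.

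**3. Does the code hide the arm?** Positions 1–10 are product and 11–20 control (2.3), so an enrolment-ordered code is equivalent to the arm label.

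**4. Where the trial stands (4. Trial Status).** 70% of 20 = 14 enrolled, so 10 product and 4 control under the allocation rule. 55% of 20 = 11 with final samples, so at least 11 − 4 = 7 of these are product patients, if there are no replacements.

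**5. Illustration: a shift aligned with arm.** Inputs: 10 per arm (2.3); two-sided 0.05 (2.8 gives 0.05; two-sided is assumed); a between-run shift of d SD fully aligned with arm (assumed). Rejection probability from the noncentral t with 18 degrees of freedom and noncentrality d × √(10/2):
- d = 0.5: 0.5 × 2.236 = 1.118, probability 0.185
- d = 0.8: 0.8 × 2.236 = 1.789, probability 0.395

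Partial alignment would give less. A shift shared by all of one patient's stools cancels from the within-patient change in an alpha-diversity index.

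**6. Illustration: open choice of outcome.** Probability of at least one p < 0.05 with no true effect:
- Four independent measures: 1 − 0.95⁴ = 0.186; six: 1 − 0.95⁶ = 0.265
- Six equally correlated measures: about 0.24 at correlation 0.3 and 0.17 at 0.7
- Simulation, 10 per arm, the number of measures set to the four named diversity measures, t-test: 0.158 at correlation 0.5, 0.120 at 0.8, 0.098 at 0.9. Adding free choice between t-test and Mann–Whitney: 0.178, 0.134, 0.111

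All correlations are assumed. These rates describe outcomes that are not fixed. A two-sided p-value is the same whether the groups are called product and control or A and B, so the rates do not measure harm from unblinding.

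**The case against.** **A reader might infer that the protocol waives all blinding, including that of the laboratory and the analyst.** The text does not support that. Section 2.6 names investigators and patients only, and gives patients a different reason. On laboratory and analyst the article is silent, and labelling and run order are details an article commonly leaves to the full protocol or a laboratory manual. Silence alone would be no finding. What remains is a stated rule resting on a stated reason that the same article undercuts.

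**The Discussion is open about the limitation and calls the design exploratory.** True, and it speaks of missing placebo and blinding together, which is wider than investigator blinding. This softens the conflict, but leaves the reasoning in 2.6 uncorrected.

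**The taxa, ratios and tests may be fixed in a document not shown.** This stands. They are not raised as separate omissions; they show only why objectivity does not settle the matter.

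**Masking does not stop someone choosing the smallest p-value, and does not remove batch differences.** Correct on both counts. Fixing the choices does the first and allocation to runs does the second, which is why the fix contains all three.

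**Alignment of run with arm is hypothetical.** Also correct. The article says samples are stored at the company, not that they are run on arrival. Each patient gives stools at three times and reversal timing depends on chemotherapy, so collection periods can overlap between arms.

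**Conclusion.** The point holds in limited form. The reason 2.6 gives for dispensing with investigator blinding is not sufficient, the Discussion says as much, and the two should be reconciled. The allocation scheme makes masking of laboratory and analyst more useful than usual, because order and dates disclose the arm.

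The size of any bias cannot be derived from the document. The 19% and 40% figures rest on assumed shifts of 0.5 and 0.8 SD fully aligned with arm. The 17–24% range rests on six measures with assumed correlations of 0.7 to 0.3 and reflects unfixed outcome choice. Neither should be read as the trial's actual error rate or as the effect of unblinding.

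This is a worthwhile, low-cost improvement in a pilot of 20 patients. It would not remove the selection bias and confounding from sequential allocation that the Discussion already concedes.

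**What to change.** Reword 2.6 along these lines:
- Patients and treating staff are unblinded.
- Stool and blood samples carry randomly assigned codes. Codes do not follow enrolment order, and enrolment order and dates are withheld from the laboratory and the analyst.
- Each patient's stools are sequenced together, with patients of both arms spread across runs, or all samples go into one run. For samples already sequenced, the analysis includes a run term.
- The analyst works on masked arm labels until the taxa lists, ratios, leading measures and tests are fixed. Since masked labels alone do not prevent selection, these should be written down before any comparison between groups is run.
- The clause stating that objective data deal with any impact of unblinding is deleted, so that 2.6 agrees with the Discussion.

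**Cost.** Relabelling, an instruction to the company that already stores and assays the stools, and some delay to sequencing. This is low cost, not free. With 11 of 20 final samples collected at the time of writing, part of the run allocation may come too late, and the run term is then only a partial remedy: if a run holds one arm only, it cannot separate run from arm. Nothing in the change touches patient care.

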### 2.7. Data Collection and Management

All investigators will receive uniform annual training to ensure consistent assessment. A professional company performing laboratory work on fecal microbiota tests will ensure high reliability and validity. Detailed contact preferences will be collected, followed by text messages before follow-up visits to promote participant retention. A participant will be considered lost to subsequent assessment after a maximum of four contact attempts have been made.

The researcher responsible for outcome management will enter data into paper-based case report forms (CRFs). The CRF data will be meticulously reviewed for completeness and accuracy. Any discrepancies identified during the review will be resolved by the principal investigator’s verification. All CRFs will be stored in a locked, secure location accessible only to research team members. Furthermore, regular audits will be conducted to monitor access and ensure compliance with security protocols. The participant’s personal information will be protected by assigning a study identification number not associated with their identity.

The collected stool samples will be safely stored at the designated company. Upon additional request within a specified period, the following analyses can be performed and utilized in future research: calprotectin analysis using enzyme-linked immunosorbent assay, characterization of short-chain fatty acids through gas chromatography-mass spectrometry analysis, and β-glucuronidase activity analysis using fluorescence assay.

### 2.8. Statistical Methods

To compare categorical variables, the χ^2^ or Fisher’s exact test will be applied, while continuous variables will be examined by conducting Student’s *t*-test or the Mann–Whitney U-test. To evaluate statistical significance of alpha and beta diversities, the Kruskal–Wallis test and permutational multivariate analysis of variance (PERMANOVA) will be performed. A *p*-value of less than 0.05 will be considered statistically significant for all variables with. Statistical analyses will be conducted using SPSS version 27.0 (IBM Inc., Armonk, NY, USA).

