## Abstract

**Background**: The gut microbiome is crucial in sustaining intestinal balance and general health. Following rectal cancer surgery, the creation of a diverting stoma to protect the anastomosis results in a defunctioned colon, leading to dysbiosis. The effect of probiotic intake on gut dysbiosis following ileostomy repair remains uncertain. Thus, this study aims to determine the changes in gut microbiota based on the intake of probiotics after diverting stoma repair. **Methods**: This single-center, parallel, prospective pilot study will include patients with primary rectal cancer planning to undergo a diverting stoma during rectal cancer surgery. The study will comprise 20 patients, with 10 patients receiving synbiotics after stoma repair and 10 patients not receiving probiotics. The primary endpoint is the change in the gut microbiota of the resting colon based on the intake of probiotics, assessed through fecal testing at the following time points: before bowel resection, immediately after diverting stoma repair, and 3 weeks after diverting stoma repair. Changes in gut microbiota will be evaluated using alpha- and beta-diversity analyses based on 16S rRNA sequencing of fecal samples. **Discussion**: This study is the first prospective cohort trial investigating changes in the gut microbiota of the resting colon based on oral probiotic administration in patients undergoing diverting stoma repair. This trial is anticipated to clarify the impact of probiotic intake in these patients. **Trial registration**: Clinical Research Information Service (CRIS) of the Republic of Korea, KCT0008392, Registered on 27 April 2023.

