## Figures and Tables

**Figure 1 jcm-14-07190-f001:**
[figure not shown]
Flow diagram of the study protocol.

**Table 1 jcm-14-07190-t001:** Schedule of assessments, interventions, and follow-up.

	Study Period			
	Enrolment	Post-Allocation		Close-Out
Time Point	t1	t2 (Before Rectal Resection)	t3 (After Ileostomy Repair)	t4 (Outpatient Visit)
Enrolment:				
Eligibility screen	X			
Informed consent	X			
Allocation	X			
Interventions:				
Probiotic intake				
Standard care				
Assessments:				
Fecal testing		X	X	X
Serum laboratory test *	X		X	X

* Complete blood count (neutrophil, monocyte, lymphocyte, hemoglobin, platelets), albumin, and C-reactive protein.

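### Section 2.8 names Kruskal–Wallis and PERMANOVA for an outcome that is within-patient change over three stools, and no named analysis uses the pairing or specifies the between-arm comparison of change

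*Protocol article*

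**What the plan says.** Section 2.5 (Outcomes) defines the primary outcome as change in the microbiota by probiotic intake, measured "at the following time points: before bowel resection, immediately after diverting stoma repair, and 3 weeks after diverting stoma repair". Table 1 labels these stool samples t2, t3 and t4. Section 2.5 also states the question: "We will analyze the pattern of changes to evaluate whether a 3-week course of probiotics alleviates dysbiosis, observed after ileostomy repair". It adds a comparison with the composition found before the first operation.

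The Abstract gives the size: "The study will comprise 20 patients, with 10 patients receiving synbiotics after stoma repair and 10 patients not receiving probiotics". Section 2.3 reports that "a sample size calculation was not performed" and that "the first 10 consecutive patients will be assigned to the probiotic group, while the next 10 patients will be assigned to the control group".

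Section 2.8 (Statistical Methods) gives the test for each kind of variable. For the diversity measures: "To evaluate statistical significance of alpha and beta diversities, the Kruskal–Wallis test and permutational multivariate analysis of variance (PERMANOVA) will be performed". Student's t-test or Mann–Whitney is named for continuous variables in general, and significance is declared at p below 0.05. The section names no paired test, change score, baseline adjustment, mixed model or arm-by-time term. It does not say which groups the Kruskal–Wallis test compares, whether stools from different times enter the same test, or how PERMANOVA permutes.

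**The concern.** The question in Section 2.5 is whether the change from t3 to t4 differs between arms. Answering it needs an analysis that links a patient's stools to each other and compares the change between arms. The univariate test committed to for alpha diversity does neither by itself.

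Kruskal–Wallis is the extension of the two-group rank test to three or more groups. With two arms and three times, its natural multi-group uses are across the three times or across the six arm-by-time cells. Both treat stools from one patient as if they came from different people. Pooling each arm's stools into one two-group test does the same.

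At stake is whether the primary result could be a false positive from pooled stools, a missed time course within an arm, or a surgical time course read as a synbiotic effect. Section 4 reports final samples from 55% of participants at 28 August 2025, and Section 2.6 leaves investigators unblinded. An open choice among these analyses could therefore be made with data in view.

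**Working it through.** **No plan figure to reproduce.** The protocol gives no effect size, standard deviation or power, so the check is of the error rates of the named test under each way it could be used.

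**Inputs from the document.** 10 patients per arm (Abstract); 3 stools per patient, so 20 × 3 = 60 stools if complete (Sections 2.3 and 2.5); nominal level 0.05 (Section 2.8).

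**Assumptions not in the document.** Normal data with equal correlation ρ between any two stools from one patient, at ρ = 0.3, 0.5 and 0.7. Simulations used 3,000 to 5,000 runs.

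**1. Comparing arms on all 60 pooled stools, no effect.** The variance of an arm mean is inflated by 1 + (3 − 1)ρ = 1.6, 2.0, 2.4. A nominal 5% test then has a true size of about 2 × [1 − Φ(1.96/√(1 + 2ρ))]:
- ρ = 0.3: 1.96/1.265 = 1.55, size 12.1%
- ρ = 0.5: 1.96/1.414 = 1.39, size 16.6%
- ρ = 0.7: 1.96/1.549 = 1.27, size 20.6%

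Simulated Kruskal–Wallis agrees: about 12, 17 and 20 to 21%.

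**2. Comparing the three times within one arm, no time effect.** Differences between times vary only with the within-patient part, (1 − ρ) of the variance, while the test scales by the whole. The statistic is roughly (1 − ρ) times a χ² on 2 df, so the size is about 0.05^(1/(1−ρ)) = 1.4%, 0.25% and 0.005%. With ten patients the simulated sizes are a little higher: about 2, 0.7 and 0.1%. The test is too conservative. For an assumed course of 0, −1, −0.5 SD, power at ρ = 0.5 is about 35%, against 58% for Friedman. The gain depends on ρ: at 0.3 it is about 40% against 45%, and at 0 Friedman is worse (34% against 43%).

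**3. Comparing all six arm-by-time cells.** With no time course the test rejects 3 to 4%, close to nominal. With the 0, −1, −0.5 SD course in both arms and no synbiotic effect, it rejects about 55% at each ρ. A significant result would say nothing specific about the synbiotic.

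**4. Comparing arms on one value per patient.** Mann–Whitney at a single time has simulated size of about 4 to 5%, and so has Mann–Whitney on the t3-to-t4 change. Both are valid, and the second addresses the stated question directly.

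**5. PERMANOVA, only if samples are permuted freely.** For arm on all 60 stools, three simulations with differing settings gave 24 to 32%, 44 to 52% and 56 to 60% false positives at ρ = 0.3, 0.5 and 0.7. In the one that also tried patient-respecting schemes, permuting whole patients for arm gave 3 to 6% and permuting within patient for time gave 2 to 6%.

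**6. Reading the arms separately.** If both arms change equally by 1 SD from t3 to t4, exactly one arm is significant in about 50% of trials with an unpaired test. Pairing does not cure this: with an equal 0.8 SD change and ρ = 0.5, a paired Wilcoxon test gave 47%.

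**The case against.** The strongest reply is that the article never says stools will be pooled or permuted freely. Section 2.5 defines the outcome as changes, so a rank test on each patient's change is open under the text and would be valid. PERMANOVA can carry an arm-by-time term and patient-restricted permutation, and a condensed article may leave such detail to a fuller document. This stands, and it limits the point. The error rates in steps 1 to 3 and 5 are conditional on how the tests are used.

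Three stronger readings are tempting, and the documents support none of them:
- **That PERMANOVA is unrestricted.** No permutation scheme is stated either way.
- **That the t-test and Mann–Whitney are the plan's tests for the primary outcome.** Section 2.8 assigns them to continuous variables in general.
- **That only a single-time comparison is valid, or that the arm-by-time question cannot be tested.** A change-score test is valid and does test it; what is missing is any statement that it will be done.

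The correlations are also assumed. Resection, diversion and possible chemotherapy lie between t2 and t3, so that correlation may be low, and the effect on error rates shrinks with it.

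Finally, this is a 20-patient pilot that calls its own design exploratory. That lowers the power one should expect. It does not excuse a test that ignores pairing, because Section 2.8 still declares significance at 0.05. Nor is this only missing detail: the protocol commits alpha diversity to a named test whose natural uses here do not fit the endpoint.

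**Conclusion.** The point holds in a limited form. Section 2.8 commits a within-patient change outcome to Kruskal–Wallis and PERMANOVA, with no named analysis that uses the pairing or specifies the between-arm comparison of change. If stools from several times enter one Kruskal–Wallis test, it is anti-conservative for arm, over-conservative for time within an arm, or responsive to the surgical time course instead of the synbiotic. The sizes in the working rest on 10 patients per arm, normal data with equal correlation of 0.3 to 0.7, and, for power and the six-cell test, an assumed time course. They illustrate what could happen and do not predict this trial's error rate. Inflation of PERMANOVA rests on the further assumption of free permutation.

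**What to change.** Amend Section 2.8, before the outcome data are analysed, to state:
- **Alpha diversity, primary test:** one between-arm comparison of each patient's t3-to-t4 change, with a 95% confidence interval. Acceptable forms are Mann–Whitney on the change, ANCOVA of t4 on t3, or a mixed model with a patient random effect and an arm-by-time term. Choose one in advance. Because allocation is sequential and not randomised, note that change-score and ANCOVA estimates can differ.
- **Within-arm time course, if wanted:** Friedman or Wilcoxon signed-rank.
- **Beta diversity:** PERMANOVA with permutation within patient for time, and of whole patients for arm and arm-by-time.
- **Interpretation:** base the synbiotic conclusion only on the between-arm contrast, not on one arm reaching significance and the other not.

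The cost is wording and slightly more analysis work. No new data or patients are needed.

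### For alpha diversity, section 2.8 fixes Kruskal–Wallis, which cannot adjust, although arms filled by enrolment order may differ in chemotherapy before stoma repair

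*Protocol article*

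**What the plan says.** Section 2.8 of the protocol article states that for alpha and beta diversity "the Kruskal–Wallis test and permutational multivariate analysis of variance (PERMANOVA) will be performed". For other data, "continuous variables will be examined by conducting Student’s *t*-test or the Mann–Whitney U-test". It names no covariate, stratum or model, and does not say whether the diversity tests use third-stool values or changes.

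Section 2.3 sets the allocation: "the first 10 consecutive patients will be assigned to the probiotic group, while the next 10 patients will be assigned to the control group". The same section makes the timing of reversal depend on whether chemotherapy is needed, and starts the product at the second stool, after the repair.

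Under section 2.5 the primary outcome is change in the microbiota over three stools. As a secondary outcome, "gut microbiota composition will be compared between patients who underwent chemotherapy before stoma repair and those who did not".

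The Discussion says of sequential allocation that "it carries the potential for selection bias and confounding, which should be acknowledged when interpreting the findings". It names neither chemotherapy nor any analytic control.

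**The concern.** The secondary comparison can only be made if chemotherapy before repair is known for every patient. The variable is fixed before the first sachet, so adjusting for it cannot absorb any product effect. It is also tied to reversal timing, hence to how long the colon is defunctioned, which the Background describes as the source of the dysbiosis under study.

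Nothing in the allocation balances it. Yet the test named for alpha diversity has no place for it. If the arms differ in chemotherapy, and chemotherapy affects the index being compared, part of that difference appears as a synbiotic effect or hides one. If the arms happen to balance, the spread that chemotherapy causes between patients stays in the error term.

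**Working it through.** **Inputs.** From the document: 10 v 10 patients (Abstract); a 0.05 threshold (section 2.8), taken as two-sided; no planned effect or power to reproduce, since "a sample size calculation was not performed" (section 2.3). Assumed, because the document gives none of them: chemotherapy rate 30–70%; chemotherapy effect 0.5, 1.0 or 1.5 SD on a diversity index; correlation between second and third stools 0.3–0.7; normal errors with SD 1.

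**1. Scale.** The difference detectable with 80% power at 10 v 10 is (1.96 + 0.84) × √(2/10) = 1.25 SD by the normal approximation, and 1.325 SD for a t-test on 18 degrees of freedom.

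**2. Chance imbalance.** Take two independent Binomial(10, p) counts with p = 0.3, 0.5 and 0.7.
- P(difference of 3 or more) = 0.22, 0.26, 0.22.
- P(difference of 4 or more) = 0.085, 0.115, 0.085.

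This treats both arms as drawn from one population. Filling one arm after the other over more than two years could make imbalance more likely.

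**3. Third stool alone, 7/10 v 3/10, no product effect.** Bias = chemotherapy effect × difference in share = 0.4 × (0.5, 1.0, 1.5) = 0.20, 0.40, 0.60 SD. In 20,000 simulated trials Kruskal–Wallis rejected in 6.4%, 9.4% and 13.2%. A linear model with arm and chemotherapy rejected in 4.8%, 5.0% and 5.0%. If only half the effect remains at the third stool, the bias halves to 0.10–0.30 SD, which brings the lower end near 5%. The range is therefore about 5–13%.

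**4. Change from second to third stool, same imbalance.** Chemotherapy before repair precedes both stools, so a stable effect cancels: bias is about 0 and rejection about 4–5%. If half the effect fades by the third stool, the bias has size 0.4 × (0.25, 0.50, 0.75) = 0.10, 0.20, 0.30 SD, in the opposite direction, and rejection is about 4–8%. The top depends on the correlation, and simulations over 0.3–0.7 reached 9.7%. At correlation 0.7 the SD of a change is √(2 × 0.3) = 0.77, so 0.30 SD is 0.30/0.77 = 0.39 of it. That is close to the 0.40 case in step 3, which rejected in 9.4%.

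**5. Second stool as a covariate.** With arm and second stool but no chemotherapy term, rejection at 7/10 v 3/10 was 4.6–7.2%, with bias mostly under 0.2 SD and at most 0.28 SD. Adding chemotherapy gave 4.1–5.6%.

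**6. Power, product effect 1.325 SD.**
- With 5/10 v 5/10 treated and third stools only, Kruskal–Wallis had 76%, 70% and 58% power for the three chemotherapy effects. A chemotherapy-adjusted model had about 80%, or about 77% on ranks.
- Separately, with no chemotherapy effect, a second-stool covariate multiplies the error variance by 1 − ρ². That is 0.91, 0.75 and 0.51 at ρ = 0.3, 0.5 and 0.7. Power rises from 80.0% (18 degrees of freedom) to 83.3%, 89.7% and 97.4% (17).
- The second stool already carries a stable chemotherapy difference. Once it is in the model, the chemotherapy term adds little power.

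**7. Price in precision.** The model has 20 − 4 = 16 residual degrees of freedom instead of 18. At 7/10 v 3/10 the correlation of arm with chemotherapy is 0.4, so the variance of the arm estimate is multiplied by 1/(1 − 0.16) = 1.19. At 8/10 v 2/10 the multiplier is 1/(1 − 0.36) = 1.56.

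**The case against.** Four arguments have weight.

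- **The outcome is change.** A stable chemotherapy effect drops out of a change score, and the second-stool covariate does most of the remaining work. This stands and limits the size. It does not remove the point, because section 2.8 ties no test to change scores and chemotherapy could still affect recovery after repair.
- **The false-positive figures are conditional.** A reader might infer that the trial's error rate is 6–13%. The documents do not support that: those figures belong to a chosen imbalance and a third-stool comparison. Averaged over chance imbalance with equal rates in both arms, Kruskal–Wallis rejected in 4.8–5.7%. Systematic drift between the two enrolment periods is plausible but cannot be sized from the article.
- **A condensed article leaves model terms to fuller documents.** This stands for PERMANOVA, which accepts covariates. A reader might infer that it will contain only the grouping, but section 2.8 says just that it will be performed. It does not stand for Kruskal–Wallis: an analysis plan that adjusted alpha diversity would have to replace the named test.
- **Confounding is admitted and the study is a pilot.** True, but an admission does not replace an adjustment that uses data already needed for the secondary outcome.

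A reader might also infer that the plan asserts an effect of chemotherapy on the microbiota. It only says that the two groups will be compared.

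**Conclusion.** The point holds for alpha diversity and is modest in size. The named test cannot adjust for a pre-treatment factor that the plan needs for every patient, in arms that nothing balances. Under the assumed rates and effects, a 7/10 v 3/10 imbalance gives about 5–13% false positives if only third stools are compared. On change scores the figure is about 4–8%, a little higher if the stools are strongly correlated, and bias arises only if the chemotherapy effect shifts between the second and third stools. For beta diversity the article fixes nothing wrong; the chemotherapy term there is a matter of specification. Adjustment handles this one factor. It does not remove calendar-time or other confounding from sequential allocation, so the comparison remains exploratory.

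**What to change.** In section 2.8:

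- For Shannon and Simpson, replace Kruskal–Wallis in the arm comparison with a linear model (on ranks if skewed) of the third-stool value on arm, the patient's own second-stool value and chemotherapy before stoma repair (yes/no).
- Where PERMANOVA compares arms on Jensen–Shannon or generalized UniFrac distances, enter chemotherapy before arm, or use marginal tests, and report the arm term.
- Keep the unadjusted result as a sensitivity analysis and tabulate chemotherapy by arm.
- State that the adjusted result is exploratory and does not correct for sequential allocation.

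The cost is a change of wording and a few lines of code, run in software that allows covariates in PERMANOVA. No new patients or samples are needed. The statistical price is two degrees of freedom and a wider interval if chemotherapy is strongly imbalanced. Section 4 reports final samples from 55% of participants at 28 August 2025 (0.55 × 20 = 11), so at that date the change could still be specified before the data were complete.
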